### Determination of sample size

The determination of sample size is dependent on the definition of the statistical unit of interest, the estimated incidence of triggers in the study population and a hypothesis about the effectiveness of the intervention.

#### Statistical unit

The main aim of this study is testing the change in adherence to the automatically verifiable CRs compared to the adherence at baseline of GPs, in terms of the mean pass rate of the rules, and the pass rate per rule. These CRs belong to different domains of geriatric care. Therefore, it is meaningful to consider a relevant subset of the selected verifiable CRs as the main statistical unit in order to calculate the sample size. This means that we eventually aim at increasing the average of the adherence to these CRs.

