### Baseline measurements

Baseline adherence to automatically verifiable CRs will be based on data elements residing in the central EMR database of the primary care centers in GAZO (EMRs of the GAZO centers are maintained by an external central server). We will measure baseline adherence based on at least 24 months prior to the use of the CDSS.

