#### Bias control and randomization

Randomization will take place after measurement of baseline data. Every CR will be randomized into two groups of GP teams. Recall that while a patient will usually be seen by only one GP, a GP team consists of two or three GPs sharing care for the same sub-population of patients. When a patient’s official GP is absent, another GP from the team may see the patient.

Based on the baseline measurement and the expected room for improvement, randomization at the GP level is the most appropriate choice in terms of power and also practicality. However, this randomization choice will be adapted in order to control for possible contamination and biases. The discussion below pertains to verifiable CRs because they are the most prone to contamination.

We assume that contamination between GPs, especially in the same center, is relatively high when some GPs receive support for a rule (intervention) and the others none (control). To reduce the probability of this kind of contamination we have two groups of GPs, A and B. Every GP in group A will receive support for a specific subset of supported CRs (subset A) and no support for the rest of the CRs (subset B). By the same token, Every GP in group B will receive support for subset B and no support for subset A. This means that for about half the CRs (subset A) the GPs in group A form the intervention group and the GPs in group B form the control group, and vice versa for the CRs in subset B. All GPs will hence receive some kind of support, which means they do not have to feel that they are in the control group. A disadvantage of this approach is that some CRs are inter-related and improvement in one can explicitly or implicitly lead to improvement in the related one, even if it is not supported. For example, if one CR is supported by giving a reminder to order a laboratory test, and the same laboratory test is required by another CR that is not supported, ordering the laboratory test will be registered as adherence to both CRs. Therefore we will group all inter-related subsets of CRs in either subset A or subset B, elements of the inter-related subsets will hence never appear in both groups.

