### Outcome measure

The main outcome measure is the degree of adherence to the automatically verifiable clinical rules (regardless of placement of GPs in teams or centers). Adherence will be calculated in the following ways: 1) as the first primary outcome measure, on which the trial will be powered, we will calculate adherence in terms of the mean pass rate, without distinguishing between specific rules. For this outcome we simply divide the number of times any rule was followed by the number of times any rule was eligible to be followed; 2) we will calculate the pass rates for each rule separately as the second primary outcome measure. The pass rate of a rule is the proportion of times that a rule was followed when it was eligible; and 3) as a secondary outcome we will calculate the number of rules for which there was effect (the pass rate of a rule in its corresponding intervention group was different than in its control group).

We will also calculate the abovementioned measures per patient. Measures pertaining to fall prevention and management will also be investigated separately because fall management comprises a distinct project in itself.

The main outcome measure for the non-verifiable CRs is the degree of adherence as reported by the GPs themselves. In particular, upon receiving advice the GPs can indicate whether they agree (and hence adhere) or disagree (and hence not adhere) with the advice. Adherence will be calculated in the following ways: 1) adherence in terms of the mean pass rate as the first primary outcome measure; 2) adherence for each rule separately, as the second primary outcome; and 3) the number of rules for which there was effect, as a secondary outcome.

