### Statistical analyses

Because the included CRs in each trial are not comparable, we do not compare the result of the verifiable CRs trial with the non-verifiable CRs trial. During the analysis plan we therefore did not consider the dependency between the hypotheses behind the two types of trials. The chi-square test will be used to compare individual and sets of CR pass rates between the supported and non supported automatically verifiable CRs, and between the CRs with advice that was framed differently (AP and IN). The binomial test will be used to test whether the number of supported CRs had higher pass rates than the non supported CRs. Statistical analyses will be performed with the R statistical software (R Foundation for Statistical Computing, Vienna, Austria). Standard statistical tests will be used to compare the baseline characteristics of the centers and patients.

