### Time line

Table 1 shows the sequence of steps in the project. It started in September 2013, will need at least 6 months of trial, and we plan to report the results in the third quarter of 2014 or first quarter of 2015.

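### In the verifiable-rule trial the main aim is worded as change from baseline, but the outcome, sample size and test are a between-group comparison that leaves measured baseline adherence out

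*Protocol article*

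**What the plan says.** All references are to the protocol article.

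- **Aim.** Statistical unit describes the main aim as "testing the change in adherence to the automatically verifiable CRs compared to the adherence at baseline of GPs", in terms of the mean pass rate and the pass rate per rule.
- **Baseline.** Baseline measurements: "We will measure baseline adherence based on at least 24 months prior to the use of the CDSS". This covers the automatically verifiable rules. Bias control and randomization adds: "Randomization will take place after measurement of baseline data".
- **Outcome.** Under Outcome measure, for the first primary outcome, "we simply divide the number of times any rule was followed by the number of times any rule was eligible to be followed". There is no baseline term.
- **Sample size.** Hypothesis about the efficacy of the intervention assumes 40% adherence in the control group and an absolute gain of 10 points in the intervention group relative to control. This gives 408 cases per group.
- **Test.** Statistical analyses: "The chi-square test will be used to compare individual and sets of CR pass rates between the supported and non supported automatically verifiable CRs". The only baseline comparison named there is "Standard statistical tests will be used to compare the baseline characteristics of the centers and patients", which does not concern the effect on adherence.
- **Duration.** Time line says the project "will need at least 6 months of trial".

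**The concern.** The stated aim and the stated analysis answer different questions. Change against the GPs' own baseline is a before-after quantity. The difference between supported and unsupported pass rates at follow-up is the randomized quantity. As written, no planned test addresses the sentence that defines the main aim, and the final report would have to depart from one of the two statements.

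The second part is lost precision. The 45 GPs work in pairs or triplets, so roughly 15 (45/3) to 22 (45/2) teams are randomized. With so few units, chance differences between the groups matter. A team's earlier adherence to the same subset of rules is a natural covariate, and the plan already has the data to compute it.

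This is not detail left to an analysis plan, because the article itself fixes both the aim and the test.

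**Working it through.** **1. Reproduce the plan's figure.** Inputs from the article: 40% against 50%, two-sided 0.05, power 0.80.

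Uncorrected: n = [1.96·√(2·0.45·0.55) + 0.842·√(0.24 + 0.25)]² / 0.10² = 387.3.

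Continuity-corrected: (387.3/4)·[1 + √(1 + 4/(387.3·0.10))]² = 407.1, rounded up to 408.

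This matches exactly. The plan is sized for a comparison of two independent groups, with no baseline term.

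**2. Set the sections side by side.** Statistical unit: change from baseline. Outcome measure, the sample size and Statistical analyses: supported against unsupported at follow-up. Apart from description, baseline adherence serves planning only: it supports the 40% control rate and the choice of randomization level.

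**3. Size of the gain from adjustment.** The article gives neither an ICC nor a baseline-to-follow-up correlation, so these inputs are assumptions:

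- 20 teams (within 15 to 22). Each team is supported for one subset and unsupported for the other, so 408 cases per group means m = 408/20 = 20.4 cases per team per subset. As an alternative, m = 200.
- Team-by-subset ICC ρ = 0.05.
- r = true correlation between a team's baseline and follow-up level on the subset: 0.5 or 0.7.
- k = baseline cases as a multiple of follow-up cases. One 6-month window gives k = 1; four windows (24/6) give k = 4.

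Formulas:

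- Design effect D = 1 − ρ + mρ.
- Reliability at follow-up R_F = mρ/(1 − ρ + mρ); at baseline R_B = kmρ/(1 − ρ + kmρ).
- Proportional fall in variance = r²·R_F·R_B.

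For m = 20.4: D = 0.95 + 1.02 = 1.97 and R_F = 1.02/1.97 = 0.518. R_B = 0.518 for k = 1, and 4.08/5.03 = 0.811 for k = 4. For m = 200: D = 10.95, and R_F = R_B = 10/10.95 = 0.913 for k = 1.

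| m | r | k | Fall in variance | D after adjustment |
|---|---|---|---|---|
| 20.4 | 0.5 | 1 | 0.25·0.518·0.518 = 7% | 1.84 |
| 20.4 | 0.7 | 1 | 0.49·0.518·0.518 = 13% | 1.71 |
| 20.4 | 0.7 | 4 | 0.49·0.518·0.811 = 21% | 1.57 |
| 200 | 0.7 | 1 | 0.49·0.913·0.913 = 41% | 6.47 |

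**4. In terms of power.** Use the uncorrected normal approximation with effective n = 20m/D: power = Φ{[0.10·√n − 1.96·√(2·0.45·0.55)] / √0.49}. For m = 20.4, an analysis that respects teams but ignores baseline has power 0.53. Adjustment raises it to 0.56, 0.59 and 0.63 in the first three rows. For m = 200, power rises from 0.78 to 0.94. The fall from 0.80 to 0.53 comes from clustering, not from omitting baseline.

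**5. Limits.** With ρ = 0, which the article's independence assumption implies, R_F = 0 and adjustment gains nothing. A raw change score is then worse: with k = 4 its variance is 1 + 1/4 = 1.25 times that of the follow-up rate alone. Adjustment is therefore the safer use of baseline.

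**The case against.** The strongest reply is that the mismatch is one loose sentence. Everything operational (outcome, sample size, test) is between groups, and that contrast is valid without any baseline term. This stands: rewording the aim alone would remove the contradiction.

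The crossed design also helps already. Every team is supported for one subset and serves as control for the other, so a team that adheres well in general contributes to both sides of the pooled comparison. This stands too. It is why the ICC in the working is a team-by-subset quantity, and only that residual variation is left for baseline to explain.

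A reader might infer more than the article supports in five ways:

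- *That an uncontrolled before-after analysis is planned, setting 24 months against 6.* No section proposes one. The unequal periods matter only for how a baseline covariate is built.
- *That baseline is never used.* It informs planning; it is absent only from the outcome analysis.
- *That the point covers both trials.* The article says baseline adherence cannot be established for the non-verifiable rules.
- *That adjustment would cut variance by 25% at the planned case count.* With r = 0.7 that takes the baseline as free of error (0.49·0.518 = 25%). One 6-month window has reliability of only about 0.52, which gives 13%.
- *That allocation should be restricted to balance baseline adherence.* Trial status reports data collection from 1 October 2013, so this appears too late.

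**Conclusion.** The point holds for the verifiable-rule trial. The stated main aim contradicts the outcome, sample size and test, and pre-randomization baseline adherence is left out of the outcome analysis. The contradiction is certain from the text. It does not invalidate the randomized comparison.

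The loss of precision is conditional, and its size cannot be derived from the article. At the planned case count it is modest under the assumptions shown (7% to 21% of variance at ICC 0.05), larger if case volume is high (about 41% at 200 cases per team per subset), and nil at ICC 0. The chi-square test's neglect of teams is a separate issue and is not counted here. The change should be made, because the data are to be collected anyway and the downside is small.

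**What to change.** 1. Reword the aim under Statistical unit as the randomized difference in pass rate between supported and unsupported teams at follow-up.
2. For the primary outcome, replace the unadjusted chi-square test, which takes no covariate, with a model that respects GP teams and adjusts for the team's baseline pass rate on the same rule subset.
3. Compute that baseline with the same case definition as the trial, using as much of the 24 months as is comparable with follow-up. Work at subset level, not rule by rule. With more than 18 verifiable rules expected (Discussion, At the level of CRs), a subset holds about 9, and 20.4/9 leaves only about 2 cases per team per rule in one window at the planned count, which is too noisy.
4. Do not substitute a raw change score for adjustment.

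The cost is a sentence of rewording, a model in place of a chi-square test, and a covariate built from an extraction already planned. The change should be fixed before follow-up adherence is compared between groups.

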#### Hypothesis about the efficacy of the intervention

A *case* is defined as the situation in which a CR is eligible, meaning that its logical condition is true. Numerous CRs from the same patient can be assessed, and eligibility cases of the same CR are considered to be mutually independent. A power calculation was performed to determine the number of cases needed to detect a minimally clinically relevant effect of the CDSS based on the previously published studies. So far, no studies have been performed that measure the level of adherence to a set of ACOVE QIs in primary care in The Netherlands but Wenger *et al*. [14] showed that a practice-based intervention in the primary-care setting had mean absolute increase pass rates of 21% (from 23 to 44%) and 15% (from 22 to 37%) in two sets of ACOVE CRs.

We assumed 40% adherence in the control group (based on our preliminary baseline analysis) in both verifiable and non verifiable CRs. We can hence make a conservative estimate of an absolute increase of 10% in the mean pass rate of the supported set of CRs in the intervention group compared to the control group. For non-cluster randomization, for a power of 0.80, and two-sided testing at the 0.05 significance level, a total of 408 cases in which CRs are eligible are required in each group.

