#### Design and implementation of the CDSS

Table 1 (Design and implementation of CDSS) shows the different steps of this second part of the project. We have developed a software module, which is not an integral part of the GPs’ electronic medical records (EMR). It forms a plug-in that interfaces with a specific EMR type. We use the same plug-in in our other trial for improving stroke prevention in patients with atrial fibrillation [11] and shortly describe it here. The CDSS plug-in can be classified [12] as active (it provides feedback without being asked to), and non interruptive (it does not interrupt the workflow of the GP). For most rules it operates in the critiquing mode (its feedback is based on deviations from the QIs) but for some rules it works in the consulting mode by providing timely advice before a decision has been made. The GPs’ EMR system includes trigger points reacting on events such as submitting a medication prescription. These triggers are: opening a patient's electronic medical record on the computer, the addition of laboratory data, changing medication, and updating the patient’s problem list. Such events will trigger sending relevant data to a remote server, called the clinical rule engine (CRE) via a secure Internet connection. This information consists of: the data buffer that holds the information entered or selected by the GP that is shown on the screen at that moment (such as selection of a medication) but is not yet saved permanently to the EMR database, laboratory data from the last 12 months, the active medication list, and a list of the patient’s diagnoses codes. The CRE evaluates the information originating from the EMR by the computerized decision rules and sends, in response, a message in an eXtensible markup language (XML) file to the CDSS plug-in on the GP’s computer. The plug-in extracts the message title from the XML file, and displays a shortened form of the title in a thin sidebar that is attached to the right side of the GP’s screen. We refer to this sidebar as the dynamic floating list (DFL) because it is updated in real-time and can be moved around on the screen. The GP can move the mouse cursor over the DFL to display the full message title and can click on it in order to open the whole message in another window. The message usually includes advice and relevant findings supporting the advice. In addition, if the GP wishes to overrule the advice, he or she also has the possibility to indicate on this window why they do not wish to adhere to the rule. Upon first appearance, the message title is displayed with a red background in the DFL, indicating that the message is new. If the GP does not open the message or does not behave according to its advice, the background will become orange the next time the GP opens the EMR, indicating the message has been shown before but not yet dealt with. For an automatically verifiable real-time rule, when the GP changes the treatment plan according to the guideline, the background will turn green and the message will then disappear. This can happen without opening the message, for example the GP might already know that he or she needs to change the treatment plan and doing so will also result in the message disappearing, without having to interact with the CDSS plug-in.

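### The primary test and the 408 cases per group assume independent eligibility cases, although cases are correlated within patients and within the randomized GP teams

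*Protocol article*

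**What the plan says.** All references are to the protocol article.

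- *Hypothesis about the efficacy of the intervention* defines a case as a situation in which a rule's condition is true. It allows several rules per patient and adds that "eligibility cases of the same CR are considered to be mutually independent". The inputs to the sample size are: "We assumed 40% adherence in the control group", "an absolute increase of 10% in the mean pass rate of the supported set of CRs", "for a power of 0.80" and "two-sided testing at the 0.05 significance level". The result is 408 eligible cases per group, stated to be for a design without clusters.
- *Outcome measure* defines the first primary outcome, on which the trial is powered: "divide the number of times any rule was followed by the number of times any rule was eligible to be followed". The second primary outcome is the pass rate of each rule. The same measures will also be calculated per patient, but no power is attached to them.
- *Statistical analyses* names the test: "The chi-square test will be used to compare individual and sets of CR pass rates". It mentions no allowance for patient or team.
- *Bias control and randomization* puts all GPs of a team in the same group. *The primary care centers GAZO* gives 45 GPs working in pairs or triplets.
- *Design and implementation of the CDSS* says that rules are evaluated when a record is opened and when laboratory, medication or problem-list data change. If a message is not acted on, "the background will become orange the next time the GP opens the EMR".

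**The concern.** The chi-square test and the sample size formula both treat each eligible case as a separate, unrelated observation. Three features of the design work against this.

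- **Team.** GPs in a team share patients and habits, and the team is what is randomized. For any one rule, a team lies wholly in the intervention group or wholly in the control group.
- **Patient.** One patient can be eligible for several rules.
- **Patient and rule.** A rule can stay eligible for a long time. In the article's own example, an anti-inflammatory drug that must be accompanied by a protective drug, the condition holds for as long as the first drug continues. If each evaluation were counted, successive cases would be near-copies of one decision. The text sets no limit per patient, visit or period.

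At stake are the type I error of both primary outcomes, the power claimed for 408 cases, and possibly the meaning of the pooled pass rate.

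**Working it through.** **Step 1: reproduce 408.** Inputs from the article: p1 = 0.40, p2 = 0.50, two-sided alpha 0.05, power 0.80, equal groups.

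n = [1.96·√(2·0.45·0.55) + 0.842·√(0.40·0.60 + 0.50·0.50)]² / 0.10², which rounds up to 388.

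With the continuity correction, n' = (n/4)·[1 + √(1 + 4/(n·0.10))]² = 97 × (1 + √1.1031)² = 407.8, that is 408. The arithmetic is right, with a design effect of exactly 1.

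**Step 2: correlated cases within a patient-rule pair.** Let m be the counted cases per pair and ρ their correlation. Neither is in the article; both are assumptions.

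- Design effect: DE = 1 + (m − 1)ρ
- Effective n = 408/DE; cases needed = 408 × DE
- Power = Φ{[0.10·√(effective n) − 1.96·√(2·0.45·0.55)] / √0.49}
- True size of the nominal 5% test = 2·[1 − Φ(1.96/√DE)]

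| m | ρ | DE | Effective n | Cases needed | Power with 408 | True size |
|---|---|---|---|---|---|---|
| 1 | any | 1.0 | 408 | 408 | 82% | 5% |
| 2 | 0.3 | 1.3 | 314 | 531 | 71% | 9% |
| 2 | 0.8 | 1.8 | 227 | 735 | 57% | 14% |
| 3 | 0.3 | 1.6 | 255 | 653 | 62% | 12% |
| 3 | 0.8 | 2.6 | 157 | 1,061 | 43% | 22% |
| 5 | 0.3 | 2.2 | 185 | 898 | 49% | 19% |
| 5 | 0.8 | 4.2 | 97 | 1,714 | 29% | 34% |

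The power formula has no continuity correction, which is why 408 independent cases give 82% and not 80%.

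**Step 3: team correlation, with no repeats at all.** From the article, 45/3 = 15 to 45/2 ≈ 22 teams, so about 8 to 11 per group. With 408 cases that is 408/8 = 51 to 408/11 ≈ 37 cases per team. The intracluster correlation (ICC) is assumed to be 0.01 to 0.05, and DE = 1 + (cases per team − 1)·ICC.

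- 11 teams, ICC 0.01: DE 1.36, power 69%, true size 9%
- 8 teams, ICC 0.05: DE 3.50, power 33%, true size 30%

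These figures describe a comparison in which each team is wholly on one side, such as a single rule or one rule subset.

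**Step 4: weighting, if every trigger counts.** Illustration with assumed figures: 20% of patients trigger 10 times with 30% adherence, and 80% trigger once with 60% adherence.

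- Share of cases from the frequent group: (0.2 × 10)/(0.2 × 10 + 0.8 × 1) = 2/2.8 = 71%
- Pooled pass rate: (2 × 0.30 + 0.8 × 0.60)/2.8 = 39%
- Mean per patient: 0.2 × 0.30 + 0.8 × 0.60 = 54%

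**The case against.** **The counting rule is not stated.** A reader might infer that every re-triggering of a rule is, by rule, a new independent case. The article does not say so. The CDSS section describes when data are evaluated and how messages are shown, and the colour scheme recognises an old message as the same one. That fits one persisting case as well as many. The independence sentence could refer to the same rule in different patients. Counting triggers is a natural reading, since the sample size section refers to the incidence of triggers, but the unit is undefined. This objection stands: the repeat figures and the weighting to frequent attenders are conditional on that reading.

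**Repeats are not separate from team clustering.** Patients belong to one GP and teams share patients, so repeats are essentially nested in teams. A team-level analysis would absorb them too. This also stands: the variance problem is one problem.

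**An undefined unit may be settled in a fuller document.** True of the unit alone. Independence and the plain chi-square test, however, are stated and would be wrong if followed.

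**The A/B design cancels some correlation.** In the comparison pooled over all rules, every team, and any patient eligible under both subsets, contributes to both sides, so an effect common to all rules partly cancels. This limits the team figures for the pooled outcome. It does not help cases of the same rule, which are the ones declared independent, or team differences specific to a rule or subset.

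**408 is a minimum.** About 6 × 7,450 × 10% = 4,470 patients are aged 65 or over, and more than 18 verifiable rules are expected, so many more cases may arise. That may help power, but it does not repair type I error. With repeats, size depends only on DE. With team correlation, DE grows as cases per team grow.

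**Per-patient measures are planned.** They answer the weighting point, but outside the powered outcome.

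**Conclusion.** The concern holds in this form: the article states an independence assumption that its own design contradicts, and it builds both the powered test and the sample size on it. The 408 is correctly computed for independent cases and for nothing else. Under the assumed 2 to 5 correlated cases per patient-rule pair with correlation 0.3 to 0.8, true size is about 9% to 34% and power with 408 cases about 71% to 29%. If each pair is counted once, this component is zero and only patient and team correlation remain. No figure here is an estimate from trial data; the document supplies neither repeats nor correlations.

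The document does not support saying that the plan prescribes counting each trigger, or that the pooled rate is in fact dominated by frequent attenders. Both depend on a counting unit that the article leaves open.

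**What to change.** 1. Delete the statement that cases of the same rule are independent.
2. Replace the plain chi-square test for the pooled and per-rule pass rates with a team-level analysis, or with a model or robust variance that allows for correlation within patient and team. With about 8 to 11 teams per group, a robust variance needs a small-sample correction.
3. State that 408 per group holds only under independence, or inflate it by a stated design effect with its assumed inputs.
4. Fix the counting unit of the primary outcome, for example one case per patient, rule and defined period or eligibility episode, so that repeated evaluations of one standing eligibility are not new cases. An episode definition keeps genuinely separate decisions, such as a second course of the same drug.

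The cost is analysis wording and a re-aggregation of logged data. Intervention and randomization do not change. There will be fewer counted cases and a less favourable stated power.

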### The primary care centers GAZO

In the Netherlands all inhabitants are enlisted with a GP, who is responsible for comprehensive health care and acts as a gatekeeper for secondary care. *Gezondheidcentra Amsterdam Zuid-Oost* (GAZO) comprises six primary care health centers in the southeast region of Amsterdam. A total of 45 GPs work in the GAZO centers (full and part-time). Every patient belongs to only one GP. However, when a GP is absent, another GP from a designated team of GPs may care for his or her patients. The team consists of pairs or triplets of GPs sharing the care of the same patients. There is an average of 7,450 (range: 3,285 to 10,055) registered patients in each center. About 10% of the patients are 65 years or older and about 5% are 75 years or older (data originating from 2009).

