Finally, although patients usually only see their own GP, the GPs do work in teams. If a patient of one of these GPs requires an immediate appointment, they may see another *paired* GP. To avoid this potential contamination, we will ensure that GPs in a team will be randomized to the same subset. As for the non verifiable CRs, group-A GPs will receive the AP (action-positive) framing, and group-B GPs will receive the IN (inaction-negative) framing. Randomization of GP teams will be concealed; a person who is not responsible for recruiting subjects and has no knowledge of the study conduct will perform it on a computer.

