### At the level of GPs

In this scenario, which is our choice, GPs will be randomly allocated for a set of automatically verifiable CRs, to one of the two groups: 1) a group receiving CDSS feedback (intervention group) and 2) a group not receiving CDSS feedback (control group). For non automatically verifiable CRs, one group will receive the AP and the other the IN framing. The advantage of this approach is the large number of individual GPs to be randomly allocated to one of the two groups; this increases power. A disadvantage is the potential contamination through the possible exchange of information between GPs within centers and within teams. In particular, for verifiable CRs the intervention-group GPs may influence those in the control group. Similarly, there might be contamination of the control-group GPs via patients that were previously seen by the intervention-group GPs, for example, because the intervention-group GP is absent or works part-time, and the patient visit is scheduled on an irregular day for the patient.

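### The 408 cases per group assume non-cluster randomisation, but GP teams are randomised, so 408 cases do not give the stated 80% power

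*Protocol article*

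**What the plan says.** The protocol article, under 'Hypothesis about the efficacy of the intervention', takes a control pass rate of 40% for both trials ("We assumed 40% adherence in the control group (based on our preliminary baseline analysis) in both verifiable and non verifiable CRs") and "a conservative estimate of an absolute increase of 10% in the mean pass rate of the supported set of CRs". It adds that "eligibility cases of the same CR are considered to be mutually independent". The result is: "For non-cluster randomization, for a power of 0.80, and two-sided testing at the 0.05 significance level, a total of 408 cases", the sentence ending "cases in which CRs are eligible are required in each group".

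The unit of randomisation is described differently in different places:

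- The Abstract (Design) randomises teams of GPs in both trials. 'Bias control and randomization' starts from GP-level randomisation, says it will be adapted, and then states that "we will ensure that GPs in a team will be randomized to the same subset".
- 'The primary care centers GAZO' gives 45 GPs and says: "The team consists of pairs or triplets of GPs sharing the care of the same patients".
- The Discussion, 'At the level of GPs', presents GP-level allocation as the chosen option and says: "The advantage of this approach is the large number of individual GPs to be randomly allocated to one of the two groups".

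The Discussion sections on centres and on clinical rules accept that few clusters cost power, and count this against those two options. Nothing similar is said about teams.

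**The concern.** When teams are randomised, cases from the same team share GPs, patients and habits, so they carry less information than the same number of independent cases. A calculation that contains neither the number of teams nor an ICC cannot give the power of such a design. The Discussion adds to the problem by claiming the power of about 45 units when the allocation rule leaves roughly half to a third of that.

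The 80% is the only power claim for either trial. If it is too high, reaching 408 cases per group could be taken as adequate when it is not, and a null result could be read as absence of effect when the trial had little chance of detecting the 10-point difference. With the number of teams fixed, a longer study helps only up to a limit.

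**Working it through.** **Inputs from the article.** Control 0.40, intervention 0.50, two-sided alpha 0.05, power 0.80, 408 cases per group, 45 GPs in teams of two or three. Teams: 45/3 = 15 to 45/2 = 22.5, so about 15 to 22.

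**Assumptions, not in the article.** ICC 0.01, 0.02 and 0.05; 20 teams as the central case; equal numbers of cases per team.

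**1. Reproducing 408.** Mean proportion 0.45.

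- Uncorrected: n = [1.960·√(2·0.45·0.55) + 0.842·√(0.40·0.60 + 0.50·0.50)]² / 0.10² = 387.3.
- With continuity correction: (387.3/4)·[1 + √(1 + 4/(387.3·0.10))]² = 407.1, rounded up to 408.

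The stated figure is therefore the continuity-corrected sample size for two independent proportions. No cluster term enters it.

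**2. Power at 408 cases per group with teams randomised.** Design effect DE = 1 + (m − 1)·ICC; effective n = 408/DE; power from the uncorrected two-proportion formula at that n (82% when ICC = 0).

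Two situations differ:

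- *Parallel*: each team is in one arm only. This covers the framing trial and each single-rule comparison. With 10 teams per arm, m = 408/10 = 40.8.
- *Crossed*: the pooled verifiable pass rate. Each team is intervention for one rule subset and control for the other, so a general team effect largely cancels and the relevant ICC is that of team-by-subset variation. With 20 teams in each arm, m = 408/20 = 20.4.

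| ICC | Parallel DE | Effective n | Power | Crossed DE | Effective n | Power |
|---|---|---|---|---|---|---|
| 0.01 | 1.40 | 292 | 68% | 1.19 | 342 | 75% |
| 0.02 | 1.80 | 227 | 57% | 1.39 | 294 | 68% |
| 0.05 | 2.99 | 136 | 38% | 1.97 | 207 | 53% |

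With 15 teams at ICC 0.05, power is 32% (parallel) and 47% (crossed).

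**3. Cases needed when the number of teams is fixed.** With k teams contributing to each arm, n per arm = 388·(1 − ICC)/(1 − 388·ICC/k). Parallel, 20 teams, k = 10:

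- ICC 0.01: 388·0.99/(1 − 0.388) = 628.
- ICC 0.02: 388·0.98/(1 − 0.776) = about 1,700.
- ICC 0.05: 388·0.05 = 19.4, which exceeds 10, so no number of cases is enough.

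The target becomes unreachable once ICC exceeds k/388. In the parallel comparison that is 7.5/388 = 0.019 with 15 teams, 10/388 = 0.026 with 20, and 11/388 = 0.028 with 22. In the crossed comparison (k = number of teams) it is 0.039, 0.052 and 0.057.

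**4. Direction of the approximations.** The powers above presuppose a test that keeps its 5% level under clustering, and they use normal quantiles. Allowing for the few degrees of freedom lowers them further: with 22 teams at ICC 0.01, the parallel power falls from 69% to 65%.

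**The case against.** Five points can be made for the plan.

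- **The condition is disclosed.** The sentence says that it refers to non-cluster randomisation, and 408 is correct on those terms. That is so. The fault lies in applying the number to this design, and disclosure does not supply the missing figure.
- **408 is a minimum.** All patients aged 65 or older in six centres are included, roughly 6 × 7,450 × 10% = 4,470, for at least six months, so many more cases may accrue. At 1,000 cases per arm and 20 teams, the crossed comparison would have about 96%, 89% and 68% power at the three ICCs, and the parallel one about 89%, 74% and 45%. This is a fair limit on the size of the problem. However, the article states no expected number of cases, and the ceiling in step 3 remains.
- **The trial is powered on the pooled verifiable pass rate, where the A/B arrangement helps.** With 20 teams the crossed comparison needs about 477 cases per arm at ICC 0.01 and 621 at 0.02, which is modestly more than 408. At 0.05 it needs about 12,300. The relief does not extend to the framing trial or to the per-rule pass rates, which are a second primary outcome.
- **The ICCs are assumed, and the required numbers use the uncorrected base of 388.** Both are true. Any positive ICC lowers power below the independent-case value. On the protocol's own base of 408, the parallel requirements rise from 628 and about 1,700 to about 680 and 2,170.
- **The GP-level passage in the Discussion is only loose wording, since the Methods describe the adaptation to teams.** This is reasonable, but the power advantage it claims belongs to a design that was not adopted.

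**Conclusion.** The concern holds. The arithmetic behind 408 is right, but it describes a trial with independent cases. For the team-randomised design, 408 cases per group give less than 80% power at every ICC examined: with 20 teams and ICC 0.01 to 0.05, 68% down to 38% where each team is in one arm, and 75% down to 53% for the pooled verifiable comparison. The exact loss is illustrative, because it depends on assumed ICCs, an inferred number of teams, equal team sizes and accrual of exactly 408 cases per group. Two conclusions do not depend on the particular ICC chosen: the stated power belongs to a different design, and with 15 to 22 teams there is an ICC beyond which more cases cannot restore it. The framing trial and the per-rule comparisons are the most exposed.

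**What to change.** Restate the sample-size section for the design in use:

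- Give the number of teams, the expected cases per team over the six months, and an ICC (with a range) estimated from the baseline EMR data, which cover at least 24 months.
- Report the resulting power, or the minimum detectable difference, separately for the pooled verifiable comparison (each team in both arms) and for the framing and per-rule comparisons (each team in one arm).
- Keep 408 only as the effective number of independent cases per group.
- Correct 'At the level of GPs' so that the team is the randomised unit and the power advantage of many individual GPs is no longer claimed.

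The cost is one calculation on data the trial is already extracting, plus text changes. No further GPs or patients are needed. The stated power will be less favourable.
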